##### Objective 1.1.b: Changes in Individual Food Groups and Food Waste

An analytical strategy similar to that used for objective 1.1.a will be followed for testing the effect of the intervention on specific food groups, including red and processed meat, fruits and vegetables, ultraprocessed foods, and dairy products, and food waste. A linear mixed model similar to that performed for the first objective will be performed, but time will be expressed as measurement days instead of weeks, thus ranging from 1 to 105. In addition to the group and subgroup analyses performed for objective 1.1.a and maximizing the higher number of observations per participant within those outcomes, individual-level models will also be used to quantify the effect of the intervention on each participant separately from the others by following an idiographic approach.

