**Methods:**

We will run a series of ABA n-of-1 trials over a year, with the first A phase corresponding to a 2-week baseline evaluation, the B phase to a 22-week intervention, and the second A phase to a 24-week postintervention follow-up. We plan to enroll 21 participants from low, middle, and high socioeconomic statuses, with 7 from each socioeconomic group. The intervention will involve sending text messages and providing brief individualized web-based feedback sessions based on regular app-based assessments of eating behavior. The text messages will contain brief educational messages on human health and the environmental and socioeconomic effects of dietary choices; motivational messages to encourage the adoption of sustainable healthy diets by participants, providing tips to achieve their own behavioral goals; or links to recipes. Both quantitative and qualitative data will be collected. Quantitative data (eg, on eating behaviors and motivation) will be collected through self-reported questionnaires on several weekly bursts spread through the study. Qualitative data will be collected through 3 individual semistructured interviews before the intervention period, at the end of the intervention period, and at the end of the study. Analyses will be performed at both the individual and group levels depending on the outcome and objective.

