##### Eating Behaviors

As shown in Figure 1, eating behaviors will be assessed daily for 15 weeks through a brief questionnaire: participants will have to report their food intake at the end of each day during the 2 weeks of the baseline period; then, every 3 weeks during the intervention period; and afterward, once per month during the follow-up period, representing a total of 105 potential measurement days per participant spread over a year (15 evaluation weeks × 7 measurement days).

A 12-item questionnaire will assess the consumption of specific food groups relevant to environmentally sustainable healthy diets as well as food waste (Table 2) [25]. The present food frequency questionnaire was designed considering the need to minimize the total number of items and make it suitable for daily assessment while adding items about relevant food groups to assess food environmental sustainability and healthiness. For each food group, the number of servings consumed during the day will be asked. Specific foods gathered in the assessed food groups will be detailed, and their serving sizes will be provided with examples that the participants can easily interpret. For instance, a serving of vegetable is reported as a medium size dish of mixed salad, cooked vegetables, or vegetable purée—1 big tomato, 2 carrots, and 1 glass of gazpacho (Figure 2). The size of a serving was established based on the Spanish Society of Community Nutrition recommendations and other Spanish documents [37,38]. The exception will be whole grains and virgin olive oil, which will be assessed in terms of their proportion among all the grains and added fats consumed during the day, respectively. The reason for assessing them as a proportion is because of the priority of healthy fat and carbohydrate intake rather than the total amount of fat and carbohydrate consumed, as the recommended amount of total added fats and carbohydrates depends on the specific energy needs of each person.

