##### Objective 1.1.a: Changes in the Environmental Sustainability and Healthiness of Diet

To test the main effect of the intervention on the environmental sustainability and healthiness of diet at the group level, linear mixed regression will be performed and expressed as measurement occasions (here, going from 1, first evaluation week, to 15, last evaluation week), using an ordered 3-categories phase variable as a fixed effect, which takes the values of baseline, intervention, and follow-up. Polynomial functions will also be fitted to the time variable to determine whether the index demonstrates any nonlinear patterns across time. If nonlinear patterns are detected, then other patterns (eg, quadratic, cubic, and piecewise) will be examined and selected based on visual inspections and goodness-of-fit indicators. Moderation analysis will be performed by exploring the role of the subjective socioeconomic level (ie, 3 socioeconomic groups entered as fixed effect) with regard to changes in diet. Fixed baseline characteristics will be included as control variables (ie, age, gender, education, income, and political orientation). Individual trajectories will be plotted, and heterogeneity in participants’ responses to the intervention will be discussed based on visual analyses using relevant guidelines for n-of-1 trials [50] (individual weekly changes in the whole diet will not be statistically modeled because only 15 observations will be available per participant).

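### Time is coded as a running count of occasions (1 to 15) or days (1 to 105) although evaluation weeks are unequally spaced, which distorts the trend, shape and time-adjusted analyses but not a phase-only contrast

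*Protocol article*

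**What the plan says.** The section on eating behaviors sets the schedule: daily reports during the two baseline weeks, "then, every 3 weeks during the intervention period; and afterward, once per month during the follow-up period". It totals these as 15 weeks of 7 days, hence 105 days per participant within the year. The abstract gives the phase lengths: 2 weeks of baseline, 22 weeks of intervention and 24 weeks of follow-up.

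The analysis section for objective 1.1.a expresses time as measurement occasions, "going from 1, first evaluation week, to 15, last evaluation week", with a three-category phase variable as fixed effect. It adds: "Polynomial functions will also be fitted to the time variable to determine whether the index demonstrates any nonlinear patterns across time". If nonlinearity appears, quadratic, cubic or piecewise forms are to be compared by visual inspection and goodness of fit.

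Objective 1.1.b uses a similar linear mixed model for the daily outcomes, except that "time will be expressed as measurement days instead of weeks, thus ranging from 1 to 105". It also promises a separate model for each participant. It states no residual correlation structure for the daily models. The model in the power simulation has a random intercept and slope per participant across time.

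**The concern.** A step of 1 on the time axis should mean the same interval everywhere. Here one occasion is one week at baseline, three weeks in the intervention and about four weeks in follow-up. The spacing changes where the phases change, so the coding can bend a straight trajectory at the points where a change of course is of interest.

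This matters because the plan draws conclusions from the shape of change. It searches for nonlinear patterns and selects a functional form by fit. In the Discussion it expects rates of change to differ between food groups and individual trajectories to be linear, stepwise or inverse-U shaped.

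In the daily data the count 1 to 105 also makes the last day of one evaluation week and the first day of the next look adjacent when they may be weeks apart. A correlation structure built on that count would treat them as neighbours. A model with independent errors would ignore that days in one evaluation week share that week's circumstances.

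**Working it through.** **1. Reproduce the plan's counts.** Baseline 2 weeks; intervention 22/3, rounded down, = 7; follow-up 24/4 = 6. Total 2 + 7 + 6 = 15 evaluation weeks, and 15 × 7 = 105 days, as stated. The phases span 2 + 22 + 24 = 48 weeks, or 48 × 7 = 336 days. A variable that ends at 105 is therefore a count of assessments, not elapsed days.

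**2. Illustrative calendar (assumption).** The timeline figure is not shown, so exact weeks are assumed: 1, 2, 5, 8, 11, 14, 17, 20, 23, 28, 32, 36, 40, 44, 48. Of the 104 steps between consecutive day numbers, 15 × 6 + 1 = 91 are truly one day. The other 13 are 15 days (7 steps), 22 days (5 steps) or 29 days (1 step), yet all are coded as 1.

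**3. Straight trend on the wrong axis.** Let the index rise by 4 points (assumption) in a straight line: y = 4 × (week − 1)/47.
- Step per occasion within the intervention: 4 × 3/47 = 0.255.
- Step per occasion within follow-up: 4 × 4/47 = 0.340.
- Ratio: 0.340/0.255 = 1.33, although the weekly rate is constant.

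Least-squares fits to these 15 noise-free values:

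| Model | Occasion 1 to 15 | Calendar week |
|---|---|---|
| Quadratic coefficient | +0.007 per occasion squared | 0 |
| Phase + linear time: intervention vs baseline | -0.22 | 0 |
| Phase + linear time: follow-up vs baseline | -0.04 | 0 |
| R² of straight line | 0.99 | 1 |

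The artefact scales with the drift and takes its sign from it: a 4-point fall would give +0.22.

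**4. Would the false curvature be declared significant?** With 21 participants, a random intercept SD of 2 (the plan's value), no random slope and a 4-point drift, the probability is 98%, 54%, 28% and 18% at residual SD 0.5, 1, 1.5 and 2. With a 2-point drift it is 54%, 18%, 11% and 8%. The article gives no residual SD, so these are ranges over assumptions.

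**5. Days within an evaluation week (conditional).** Suppose one participant's 105 days were analysed as independent while a share ICC of the daily variance belonged to the evaluation week. The variance of a phase mean is then multiplied by 1 + 6 × ICC, and the rejection rate of a nominal 5% test is roughly P(|Z| > 1.96/√(1 + 6 × ICC)).
- ICC 0.05: 1.96/√1.3 = 1.72, about 8.6%.
- ICC 0.1: 1.96/√1.6 = 1.55, about 12.1%.
- ICC 0.2: 1.96/√2.2 = 1.32, about 18.6%.

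Simulated null series (2, 7 and 6 evaluation weeks of 7 days; runs of 20,000 and 200,000) gave 8.6 to 8.8%, 12.3 to 12.5% and 19.2 to 19.5% for intervention versus baseline. The effective number of observations, 105/(1 + 6 × ICC), is about 81, 66 and 48, against the article's rule of thumb of at least 70 for individual analyses.

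**The case against.** The strongest reply is that the main test compares phases, and a phase-only contrast is the same whichever way time is coded. That stands, so a reader should not infer that the headline phase comparison is biased. The polynomials are an additional step. Even where phase is adjusted for linear occasion, -0.22 is about 11% of the 2 points per phase assumed in the power simulation (0.22/2), and under an upward drift it works against the intervention. The linear fit of 0.99 means that overall direction survives. A piecewise fit with breaks at the phase boundaries also keeps each phase straight; only the slope units differ between phases.

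A tempting stronger reading is a three- to fourfold artefact, obtained by dividing 0.255 and 0.340 by the baseline step of 4 × 1/47 = 0.085. That baseline slope is a single step between two adjacent weeks, and the article does not plan to interpret it. Between the two phases with several evaluation weeks the ratio is 1.33.

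A second is that the individual models will produce many false responders. The article does not say that days will be treated as independent. It is silent on error structure, which an analysis plan may well settle, and it gives no within-week correlation. The figures in step 5 are therefore conditional on both assumptions. The time variable itself, by contrast, is stated outright, so this part of the point does not rest on silence.

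**Conclusion.** The point holds in a limited form. The stated time variables do not fit the stated schedule, and the analyses that use time as a quantity are distorted: polynomial and piecewise shape, comparisons of slope between phases, random slopes over time, and phase effects adjusted for time. Phase-only contrasts are not affected.

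The size is moderate. On the assumed calendar with a 4-point linear drift, the artefacts are a quadratic term of about +0.007 per occasion squared, a time-adjusted intervention effect of about -0.22 and a 1.33-fold apparent steepening from intervention to follow-up. All three disappear on calendar weeks. Exact weeks, drift and residual SD are assumptions; the unequal spacing and both codings are in the article.

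The inflation of individual-level error to about 9%, 12% and 19% at ICC 0.05, 0.1 and 0.2 is a reason to write the correlation into the plan. It is not evidence that the plan makes that error.

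**What to change.** In the analysis sections for objectives 1.1.a and 1.1.b, replace the occasion count with elapsed study week and the day count with elapsed study day since start, both known from the assessment schedule. Use them in all trend, polynomial, piecewise and random-slope terms. State whether the phase effect is estimated with or without adjustment for time.

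For the daily models, including the single-participant ones, state that days within the same evaluation week may be correlated, for example through a random intercept for evaluation week (nested within participant in the group models).

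Changing the time variable needs no new data and no change in conduct. The second change costs precision: individual-level intervals become wider, and with only two baseline evaluation weeks per participant the individual baseline contrasts will be imprecise and the week-level variance poorly estimated.

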Individuals will be enrolled in the study if they meet the following characteristics: adults aged from 18 to 65 years; residing in Barcelona; speaking and reading Spanish fluently; having a mobile phone supporting the installation of a smartphone app; reporting no history of eating disorders (eg, anorexia nervosa, bulimia nervosa, and binge eating) or any food intolerance or allergy (eg, celiac disease, and nut allergy) or other chronic illnesses that might directly impact eating behaviors (eg, diabetes, cardiovascular disease, cancer, and obesity); following an omnivorous diet; and scoring ≥5 out of 10 points on the dietary questionnaire included in the Google form (refer to Multimedia Appendix 2 for the scoring criteria). The exclusion criteria are being pregnant or planning to be pregnant in the next year, being in a postnatal situation for <3 months, breastfeeding, being professional athletes, following specific diets (eg, vegan, vegetarian, high protein, slimming, gluten free, and low in sugars), reporting any illnesses that might directly impact eating behaviors, and not taking their own decisions about food choices (eg, someone else, such as husband or wife or partner or mother or father, selects what they eat for most of their meals).

Participants will receive financial incentives for their participation. Over the course of the study, there will be 15 evaluation weeks, during which some questions should be answered daily and others once a week (refer to *Measurement* section). For each evaluation week, they will receive €10 (US $10.7) if they complete at least 6 out of the 7 daily questionnaires plus the weekly assessment. Thus, in total, each participant can receive €150 (US $160.4) for full participation in the study. At the end of the study, they will receive their money through bank transfer.

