### Data Analyses

#### Sample Size and Power Analyses for the Quantitative Side of the Project

The sample size for this pilot study is constrained by financial and human resources. We plan to recruit a total of 21 participants, with 7 participants in each subjective socioeconomic group (refer to the *Participants* section). However, in terms of statistical power, we will benefit from the intensive longitudinal nature of the study, that is, 15 evaluation weeks and up to 105 daily observations per participant. For objective 1.1.a, for which a weekly environmentally sustainable healthy diet index will be used, up to 315 observations will be available in total (21 participants × 15 evaluation weeks) and 105 observations per socioeconomic group (7 participants × 15 evaluation weeks). For objective 1.1.b, for which the daily raw data will be used, up to 2205 observations will be available in total (21 participants × 105 daily assessments), 735 observations in the 3 socioeconomic groups (7 participants × 105 daily assessments), and 105 observations at the individual level (as a general rule of thumb, a minimum of 70 observations are required for conducting individual-level analyses [48]). Given the pilot nature of this trial, we conducted power simulation analyses only for objective 1.1.a (ie, change in the weekly level of food healthiness and environmental sustainability). Considering group-level analyses and the analytical strategy detailed in the next section and assuming an increase of 2 units in the environmentally sustainable healthy diet score per phase, simulated power analysis indicated an adequate power value of 96%. The simulation was performed by generating the response variable as follows:

Fixed effects: the intercept was set at 6, and the fixed coefficient for the phase was set as −2 for the initial phase and +2 for the final phase based on our average expected change in the main outcome.Random effects: it was assumed that each participant would have both a random slope and a random intercept and that both followed normal distributions, with SDs of 2 for the intercept and 0.5 for the slope. The correlation between them was set as 0.2. The random effect for each participant was created by drawing random numbers from a multivariate normal distribution whose covariance matrix was specified using these parameters (R mvrnorm from the package *MASS*).

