##### Objective 1.2: Feasibility of the Intervention

This objective will mainly be investigated through the qualitative data analyses reported in the next section. Simple quantitative analyses will be conducted to examine the relevance of our motivational and educational messages (ie, scores provided to the text messages at the individual and collective levels). We also report the percentage of missing values for each measurement burst.

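### The daily food-group models name no day-of-week term, so a shift between phases in which days are skipped could pass for a small change in diet

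*Protocol article*

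**What the plan says.** All references are to the protocol article.

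- **Daily models.** The section on objective 1.1.b states: "A linear mixed model similar to that performed for the first objective will be performed". The change of time scale is that "time will be expressed as measurement days instead of weeks, thus ranging from 1 to 105".
- **Terms carried over.** The section on objective 1.1.a describes a mixed regression "using an ordered 3-categories phase variable as a fixed effect, which takes the values of baseline, intervention, and follow-up". It adds polynomial functions of time and socioeconomic group as a moderator. It also states: "Fixed baseline characteristics will be included as control variables (ie, age, gender, education, income, and political orientation", a list in which every item is constant within a person.
- **Individual models.** The 1.1.b section also plans one model per participant, without listing its terms.
- **Schedule.** The Eating Behaviors section describes daily reporting in whole weeks, "representing a total of 105 potential measurement days per participant spread over a year (15 evaluation weeks × 7 measurement days". The sample size section counts "up to 2205 observations will be available in total (21 participants × 105 daily assessments" as the maximum.
- **Payment.** The Participants section pays €10 for each evaluation week to participants "if they complete at least 6 out of the 7 daily questionnaires plus the weekly assessment".
- **Missing data.** The section on objective 1.2 states: "We also report the percentage of missing values for each measurement burst".

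**The concern.** A daily food diary can have a weekly rhythm. A counter from 1 to 105 with low-order polynomials cannot follow it: there are 15 weekly cycles, and a cubic has at most two turning points. With whole weeks answered this does no harm to the phase contrast, because every phase has the same 5:2 mix of weekdays and weekend days. With one day missing, the mix depends on which day it was.

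A mixed model handles missing days without bias when, given the terms in the model, missingness is unrelated to the unseen value. Day type is not among the named terms. If people skip weekend days more often (or less often) later in the year than at baseline, and eat differently on those days, the phase effect absorbs the difference. A percentage missing per burst would not reveal this, since it counts missed days without saying which they were.

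The individual models matter most. One person's skipping habit is not averaged out there, and baseline supplies at most 14 days, of which 4 are weekend days.

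**Working it through.** **The plan's own counts.** 15 × 7 = 105 days per participant and 21 × 105 = 2205 in total; both reproduce. Under the payment rule 6 × 15 = 90 days suffice for full payment, so 15 of 105 can be missed without loss. Weeks per phase: 2 at baseline, 6 monthly weeks in follow-up, hence 15 − 2 − 6 = 7 in the intervention.

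**Weekend share of answered days in a week**

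- all days answered: 2/7 = 0.286
- one weekend day skipped: 1/6 = 0.167
- one weekday skipped: 2/6 = 0.333

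**False shift in the phase mean.** Let D be the weekend-minus-weekday difference in servings a day. The article gives no value, so D is assumed. The shift is D × (change in weekend share).

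- Complete weeks to always skipping a weekend day: 2/7 − 1/6 = 5/42 = 0.119, so 0.119 D a day, or 7 × 0.119 D = 0.833 D a week.
- The extreme within the 6-of-7 rule, from always skipping a weekday to always skipping a weekend day: 2/6 − 1/6 = 0.167, so 1.167 D a week.
- Same skipping in every phase: 0.

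| Assumed D (servings/day) | Complete → weekend skipped (servings/week) | Weekday → weekend skipped (servings/week) |
|---|---|---|
| 0.3 | 0.25 | 0.35 |
| 0.5 | 0.42 | 0.58 |
| 1.0 | 0.83 | 1.17 |

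As a yardstick, Table 3 runs red and processed meat, and ultraprocessed food, from 1 point to 0 over 0 to 2 servings a week. The middle column is about 12%, 21% and 42% of that range.

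**Effect on false positives.** A simulation with no true diet change used 21 participants, 2 baseline and 7 intervention weeks, a t-test on participants' phase differences and 4000 replicates. The day-level SD of 1.0 and between-person phase SD of 0.3 are assumptions. The nominal level is 5%.

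| D | Weekend day skipped in half of weeks, both phases | None at baseline, half of intervention weeks | None at baseline, every intervention week |
|---|---|---|---|
| 0.25 | 5.4% | 4.7% | 6.0% |
| 0.5 | 5.2% | 6.1% | 8.7% |
| 1.0 | 5.2% | 9.6% | 23% |

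With the known weekend difference removed, as an ideal adjustment would do, the rate was 4.9% to 5.5% throughout.

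**Residual variance.** A weekend indicator has variance (2/7)(5/7) = 0.204, so an omitted weekend effect adds 0.204 D² to the daily variance. For assumed D = 0.5 and SD 0.7: 0.204 × 0.25 = 0.051, and 0.051/0.49 = 0.10. The standard error rises by about √1.10 − 1 = 5%. This part needs no skipping at all.

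**The case against.** The case against is substantial, and most of it stands.

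- **An unlisted covariate in a condensed article is not an error.** The full analysis plan may contain a day-of-week term, and nothing in the article excludes one. This is why the point is a suggestion. It survives because the article does name the time variable and the covariates, and none of them fits a weekly cycle.
- **The design already balances days.** Bursts are whole weeks in every phase, and a report is asked for every day. A missed day is free only in terms of payment.
- **The payment rule is the same in all 15 weeks.** A reader might infer that it causes skipping to change between phases. It does not: it gives no reason for such a change, and a second missed day forfeits that week's payment. Nor does the article say that weekend days are the ones likely to be missed. If weekdays were skipped instead, the bias would reverse.
- **The 0.119 D figure is an extreme.** As a group effect it needs every participant to answer every day at baseline and to skip a weekend day in every later burst. For D up to 0.5 the simulated error rate stays below 9%.
- **The extra variance is conservative.** With complete weeks it does not bias the phase contrast; it only makes the standard error somewhat too large.

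A reader might also infer that the daily models contain phase and a day counter and nothing else. The text does not support that. The group models carry more terms, and those of the individual models are not stated.

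**Conclusion.** A worthwhile minor improvement. The named terms of the daily group models leave the phase contrast unprotected against day-selective missingness, and the planned missing-data report would not detect it. Bias requires both a real weekend difference and skipping that shifts between phases. The documents show neither, so it would go too far to say that the plan will turn skipped days into apparent diet change.

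The size is bounded: 0.25 to 0.83 servings a week for D of 0.3 to 1.0 when complete weeks give way to always skipping a weekend day, and zero when skipping is stable. The loss of precision, about 5% of the standard error at D = 0.5 and SD 0.7, is modest and matters most for the individual models with their short baseline. Every value of D, every SD and every skipping rate is an assumption. The sizes are in servings and do not cover the yes/no food-waste item.

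**What to change.** 1. Add a weekday/weekend fixed effect to every daily model of objective 1.1.b, group and individual.
2. Report phase effects standardised to a week of five weekdays and two weekend days. With one common weekend effect in a linear model, the phase contrast does not depend on this weighting, but the phase means do. The contrast would depend on it too if the weekend effect were allowed to differ by phase.
3. Extend the missing-data report planned under objective 1.2 to show missed days by weekday/weekend within each phase. This directly tests whether the concern arises, and it serves the feasibility objective.

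The cost is one model term and one table, with no new data and no change for participants. It needs the calendar date of each report. The article does not say that the app stores this, but placing reports on measurement days implies that it is known.

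The term corrects only the part of selective skipping that coincides with weekends. Skipping tied to particular occasions within a day type remains, and should be acknowledged as a limitation.
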